#### Court self-assessment (CSA)

JDTCs and TJCs are scheduled to complete a court self-assessment in spring 2018 and again in spring 2020 to describe the degree to which their “current” practices are similar or different from the 2016 JDTC Guidelines. Usually these will be completed by the JDTC coordinator or an individual serving in the same role (for the JDTC self-assessment) or a senior official in the local juvenile justice system (for TJC self-assessment), these assessments gather information across 14 content areas, including background (e.g., JDTC inception date, memoranda of understanding across partner agencies, and stages), JDTC eligibility, referral and entry procedures, risk and need assessment, composition and training of the team/staff, family and school engagement, treatment, case planning and other services provided to participants and their families, pre-hearing meetings and court sessions, court responses (e.g., incentives, sanctions, and therapeutic responses), drug testing, program/court completion or discharge, data collection, and estimates of characteristics of participants (e.g., % who use alcohol, race/ethnicity, and % who complete or are unsuccessful in the JDTC).

Embedded within the CSA are detailed questions that directly assess variables pertinent to the seven objectives (and numerous sub-objectives) outlined within the JDTC Evidence-Based Guidelines. For example, in relation to the Objective #4 (“Conduct comprehensive needs assessments that inform individualized case management”), the CSA queries whether participants are assessed for risk of reoffending using either an established risk assessment instrument (e.g., Youth Level of Service/Case Management Inventory, YLS/CMI) or less formal risk assessments, and the level of team training on these tools. Also, courts are asked whether they use needs assessments (like the Addiction Severity Index or Global Appraisal of Individual Needs), how they are used (e.g., determine eligibility, identify youth need, and identify family needs), and whether they are used to inform the development of individualized case plans for JDTC participants or other court-involved youth (TJC). Numerous possible case plan elements are queried, including type of case management and services (e.g., office-based outpatient group treatment, home-based family treatment, mental health counseling, parenting classes, and gender-specific services). The CSA also gathers information on whether the court has incorporated evidence-based interventions to address specific needs, such as Motivational Enhancement Therapy with Cognitive Therapy (MET/CBT), Functional Family Therapy (FFT), and contingency management (CM).

In addition to a gaining a deep understanding of how the court operates, the repeated administration of the CSA will enable comparisons between the baseline and follow-up CSAs to determine what changes occurred in site operations and guideline adherence over time. This comparison is important because it will provide information on whether courts adopted additional practices consistent with the JDTC Guidelines, or dropped practices they found difficult to implement and sustain.

#### Traditional juvenile court self-assessment (TJCSA)

Because assignment to condition will involve youth receiving services-as-usual via the TJC within the same jurisdictions as the JDTCs, it was imperative that the TJCs be assessed as well because many include some of the same components as JDTC, and several are a part of concurrent juvenile justice reform efforts. TJCs and JDTCs also use some of the same staff and treatment resources and staff are likely to change over time. The TJCSA was an abbreviated version of the CSA, with the sections pertinent only to JDTCs omitted.

#### Site visits

Data on the operations of JDTC and (to a lesser extent) TJC at each research site also are collected by a multi-day site visit conducted once during the study period and attended by two researchers. Site visit data are collected using two distinct measures: 1) semi-structured interviews conducted with JDTC staff and 2) observation of staffing and court operations. The visits aim to examine local adjudication processes, how the JDTC Guidelines are implemented and interpreted within local context, other specialized dockets/services (such as diversion outside the JDTC), and any unique or complex features not necessarily obtained using the CSA. Special attention is paid to understanding potential overlap between JDTC and TJC in terms of judges, community supervision staff, and substance use treatment program access, and to collecting data that may confirm or augment CSA findings. Extensive field notes are collected during each site visit, from which a lengthy report summarizing how each site operates is created. A logic model is also developed to depict how each program enrolls individuals to treatment. Logic models are developed and confirmed with each site to correct any omissions or inaccuracies.

### Primary outcomes

#### Recidivism

For this study, recidivism is measured both by self-report on the follow-up surveys, as well as through juvenile justice records abstraction which includes information retrieved from local and statewide databases on new arrests. Consistent with the OJJDP’s recidivism workgroup (Harris et al., 2011), operational definitions for recidivism will be derived separately for self-report and official records, as well as a combination of these information sources, and will focus on new arrests following assignment to study condition, with measures reflecting whether any new arrest occurred (0 = No, 1 = Yes), the number of new arrests, as well as subsets of these arrests based on major offense types including property, violent, public disorder, and substance possession (including alcohol). Specific arrest dates will be collected for each, enabling analyses to consider the latency (i.e., length of time) between study assignment and date of arrest.

#### Substance use

Substance use problems are measured using the GAIN-SS’s Substance Disorder Screener (SDScr; Dennis et al., 2006) and the number of days of substance use, both components of the youth surveys. The SDScr has five items measuring recency of symptoms related to weekly use; time spent consuming drugs; drug-related problems; reduced involvement at work, home, or school; and withdrawal. It has been recommended by the National Institutes of Health (NIH; https://www.phenxtoolkit.org/protocols/view/560102?origin =search) and Substance Abuse and Mental Health Administration (Substance Abuse and Mental Health Services Administration (SAMHSA), 2012) as one of the most reliable, valid, and efficient substance use screeners, and has been shown to be accurate for diagnosis (AUC = .9; Dennis et al., 2006) and sensitive to change, and to predict change in standardized educational test scores (Rattermann, 2014). The operational definition is percent days of use, which is calculated as the days of use in the prior 90 days divided by 90 minus any days in a controlled environment, and trimmed to stay between 0 to 100%.

### Secondary outcomes

The study also has multiple secondary outcomes, including measures of changes in internalizing and externalizing mental health symptoms, well-being (happiness, connectivity, self-worth), relationships with parents/guardians and other very important adults, peer risk and support, involvement in prosocial structure activities, and academic performance. Further information on these other measures is available in the detailed study design protocol prepared for OJJDP (Dennis et al., 2019, b).

## Discussion

Juvenile drug treatment courts (JDTC) have struggled to define themselves since their inception in 1993. Early courts followed a format similar to adult drug courts, but these clearly did not address the unique needs of juveniles, including developmentally-appropriate treatment services and the importance of working within the family environment. Developed by a consensus panel of practitioners and researchers from these earlier courts, a set of guidelines emerged detailing 16 strategies for JDTCs (Bureau of Justice Assistance (BJA), 2003). But, like the early JDTCs, research with courts following these strategies failed to provide convincing evidence that this “model” was associated with significant reductions in general recidivism or in drug use. Several meta-analyses found that JDTC impacts were inconsistent and inconclusive on general recidivism, recidivism for drug law violations, and drug use (Mitchell et al., 2012; Tanner-Smith et al., 2016a, 2016b; Wilson et al., 2019). Hybrid models of JDTCs were developed, with the most common of these hybrids being a type that incorporated the evidence-based practice, *Reclaiming Futures* (Korchmaros et al., 2015). The most recent focus has been on a new set of evidence-based guidelines for JDTCs, developed through meta-analyses commissioned by Office of Juvenile Justice and Delinquency Prevention (OJJDP), 2016. OJJDP also provided funding for a rigorous multi-site evaluation of these guidelines. This current paper presented the protocol for the Juvenile Drug Treatment Court (JDTC) Guidelines Cross-Site Evaluation project, including an in-depth description of the research design, research sites and samples, measures, and data collection protocol designed to complement the study goals and research questions.

The study is well-positioned to complete each goal and to answer each research question, by using multiple data sources and collection methods for both the program and youth levels. For example, several study goals and research questions are specifically focused on the feasibility of implementing the new guidelines and understanding whether different interpretations of the guidelines by the JDTCs are associated with better outcomes, or whether the presence or absence of specific guidelines lead to better/poorer outcomes. Therefore, it is particularly important for the study to use reliable, comprehensive measures of program implementation. The protocol uses a Court Self-Assessment survey that carefully measures the courts’ perception of whether and to what extent each of the specific guidelines were implemented, as well as a multi-day site visit during which researchers observe court operations and interview key stakeholders. The Court Self-Assessment is conducted twice, at baseline and again 2 years later. The timing of the Court Self-Assessment enables determination of whether programs change over time in their use and modification of the guidelines. It is important to know which guidelines are adopted and which are not sustained over the course of the study.

The multi-day site visit, which occur between the first and second administration of the Court Self-Assessment, provide a limited validity check of self- and researcher-ratings of JDTC implementation of specific guidelines. The site visits also allow researchers to ask questions related to assessment findings and obtain a level of detail about site-specific context and guideline interpretation not achievable via survey. The site visit may be particularly helpful for understanding changes in how the guidelines are or are not implemented because researchers are able to question the programs about the specific contexts surrounding these decisions.

Another significant benefit of the current study is that the self-assessment (absent JDTC-specific questions) is also completed for the traditional juvenile court (TJC) at each site. An unanswered question in the current literature is to what extent practices differ between co-located JDTCs and TJCs. It is unclear to what extent treatment intensity, court review, family therapy, mental health services, and drug testing will vary between JDTC and TJC. The greater the similarity between JDTC and TJC, the greater the likelihood that the evaluation will show null effects related to the outcome measures, similar to the Rio Hondo DUI Court evaluation, which found at the conclusion of a randomized controlled trial that it was not effective compared to the standard sanctions for DUI (Eibner et al., 2006; MacDonald et al., 2007). However, when looking for possible reasons for the null results, these researchers found a high degree of similarity, including treatment intensity, between the DUI court and the standard interventions, with the primary difference being the number of times offenders’ progress was reviewed by a judge. DUI court participants had a modestly higher number of contacts with the judge (Eibner et al., 2006; MacDonald et al., 2007). Knowing what differences exist in service availability and usage between JDTC and TJC sites, therefore, is paramount to avoiding erroneous null conclusions. Site visit interviews further augment CSA findings in this area.

Youth-level data collection procedures also evidence significant strengths. For example, self-reported data, much of which is typically not the part of official administrative records, will be used to collect both the primary (i.e., recidivism and drug use) and secondary outcomes (e.g., mental health and wellness), enabling direct comparisons between JDTC and TJC youth on each of these outcomes. Importantly, these self-reported data are collected using an interview that incorporates numerous instruments with known measurement properties for the same populations being studied. This approach significantly enhances confidence regarding data validity and reliability. Moreover, the interview data are collected three times during the course of the study; baseline, 6 months, and 12 months post-program entry. The use of multiple comparable time frames for these data enables comparison between JDTC and TJC youth on both primary and secondary outcomes at each time point, as well as change over time. When combined with the data on guideline implementation and the degree to which services overlap between JDTC and TJC conditions, analyses will be able to provide a clearer picture regarding the degree to which youth in each condition change (for better or for worse) while controlling for other potentially confounding variables.

Outcome data also are being abstracted from the administrative records, which include local and state-wide information for both JDTC and TJC youth. These data are valuable for comparison to the self-report data for establishing its concurrent validity. In addition, the degree to which findings observed in the self-reported data (i.e., between-group differences in recidivism and drug use) also are found in the administrative data will enhance the construct validity of research findings regarding the effectiveness of the JDTC programs. An added benefit of the administrative data is that specific event dates (e.g., date of a new arrest, date of a positive drug assay) will be recorded. This detail enables event history analysis of the relative risk ratios over time between groups and considers the unique aspects of data (e.g., censoring), as well as differences in risk ratios to specific time points (operationalizable in both days, weeks, and months) tested, such as time to first arrest, or number of days of negative drug tests.

Strong inferences regarding the effectiveness of JDTC vs TJC are made possible by the unique hybrid design used by this study. Both randomized controlled trials (RCT, two sites) and regression discontinuity designs (RDD, eight sites) are strong research designs for establishing the internal validity of the study. Equivalent JDTC and TJC groups in the RCT, for example, eliminate concerns related to selection artifacts related to pre-existing differences in the groups being studied. Similarly, whether mortality is a threat to the internal validity of the study involving differential dropout of youth between conditions (which results in non-equivalent groups by the end of the study) can and will be examined. The presence of an RDD has the added benefit of being more acceptable to judges and practitioners who may be uncomfortable with random assignment of youth to different programs/services. The RDD uses a pre-established cut-score involving both criminal and substance use histories to assign youth either to JDTC or TJC. Comparison of the expected outcomes for JDTC to the observed outcomes relative to those for the TJCs will indicate whether observed outcomes for the JDTCs more closely resemble those predicted for them or the outcomes following TJCs.

Gaining important insight needed for guiding policy and practice surrounding JDTC is a significant expectation of the current study. For example, this is one of only a handful of RCTs of JDTCs. As noted earlier, the question of the effectiveness of JDTCs remains unclear. If findings from our RCT show significant reductions in recidivism and drug use and improvement in secondary outcomes like mental health, it will provide additional support for the JDTC, complementing the RCTs conducted by Henggeler et al. (2006, 2012). This support would come at a critical time in the development of JDTCs, which have seen a 31% decrease in the number of operational programs between 2013 and 2020; that is, a decrease from 447 JDTCs in 2013 (Marlowe et al., 2016) to 308 in 2020 (National Drug Court Resource Center, 2021). The data collected from the Court Self-Assessment and the TJC Self-Assessment will provide important information about whether/how JDTCs differ from “standard of care” (i.e., TJC) when we analyze the JDTC and TJC pairs. It is important to determine whether JDTCs and TJCs represent largely overlapping models of services referral and delivery. If there is substantial overlap, if there are null findings between JDTC and TJC for reductions in general recidivism and drug use, this would seem to indicate that these largely overlapping models lead to similar outcomes. Therefore, local jurisdictions could decide between alternatives, adopting the approach that best fits with their local juvenile justice system. A deeper analysis of the variation in the implementation of guidelines, also facilitated through the CSA and TJCSA, as well as the site visits, represents, perhaps, the most substantial opportunity to draw possible implications regarding how JDTCs should be implemented to maximize youth outcomes. Practices associated with positive outcomes would provide actionable information to the field so that training and technical assistance providers, and funders, could then share information with programs and work to increase the use of the effective practices. However, because a single study alone is insufficient for conclusions, such findings also would necessitate the need for more controlled studies of specific guidelines (i.e., those found in our study to be correlated with better outcomes). Finally, this study presents a clear opportunity to revise the Evidence-based Guidelines based on the comparisons of JDTCs and TJCs and comparison of JDTCs that do/not implement a specific guideline. For example, the results can indicate which practices are more or less effective (so maybe the guidelines might be revised to emphasize some practices over others), as well as which practices are less likely to be implemented – where revisions could help possibly help provide additional guidance about how to implement the practices and/or potentially identify which practices are not feasible or practical to implement.

Limitations to the current study are related to the veracity of youth during interviews with research staff, the use of a non-random sample of JDTCs in the study, and the possibility of treatment cross-over effects between study conditions. With respect to youth self-reported data, interviews are collected by research staff trained in establishing rapport with the youth, and it is likely that youth are more comfortable with sharing information with research staff because they were told that their data are strictly confidential. The non-random sample of JDTCs presents the possibility that the sites chosen are not representative of JDTCs nationwide. JDTCs were recruited because they were sufficiently large enough to help ensure a sizable number of JDTC and TJC youth could be recruited for the study. Typically, juvenile treatment courts are quite small with fewer than 25 youth in the program. To gain insight into whether the sampled programs varied along other dimensions from what is seen nationally, survey data are available from a nationally representative sample of juvenile community supervision agencies, with a sizable number of these jurisdictions also implementing JDTCs nearly contemporaneously with the current study (Robertson et al., 2019; Scott et al., 2019). Comparing our research sites with these can provide insight into whether and how these programs differed from a larger national sample of JDTCs, giving some understanding, perhaps, into the generalizability of findings from this study. However, any examination in variations in guideline adherence in association with outcomes remains limited by the small number (*N* = 10 JDTC; 10 TJC) of programs examined. These analyses, therefore, will be discussed relative to future directions for research. For example, if implementation of a specific guideline is correlated with better outcomes, we will acknowledge this result as an important finding limited by the number of programs in the study that should be examined more precisely in, perhaps a RCT of that specific guideline among a multi-site sample of programs. Such a trial would give an unambiguous conclusion regarding the efficacy of that guideline in courts randomly assigned to adopt that guideline (or not). Finally, although some JDTCs in the current sample likely share some staff with their corresponding TJCs, it is explained and periodically reinforced with JDTC staff that if they also work with youth in the TJC condition that for the study to have a clearer basis for making conclusions, that JDTC-specific interventions should not “leak” into their work with the youth in the control condition. However, given this was applied research in real-world settings, it is likely that staff who thought JDTC practices may be useful chose to use them with the TJC youth as well. Regardless, the data that are collected from the Court Self-Assessment and the Traditional Juvenile Court Self-Assessment will give keen insight into the extent to which JDTCs and TJCs differed in their approaches and services delivered. Therefore, we will be able to see the extent to which apples-to-apples or apples-to-oranges comparisons are being made between study conditions at each study site.

In conclusion, strengths associated with the data collection tools and research designs have equipped the current study, the Juvenile Drug Treatment Court (JDTC) Guidelines Cross-Site Evaluation project, to address each of its goals and answer all research questions. The use of both program- and youth-level data permit the assessment of variations in guideline adherence, enabling testing of these practices in relation to youth outcomes. Having multiple types of implementation data strengthens confidence in the degree to which programs and researchers rate adherence to these guidelines. Comparison of JDTC and TJC youth from all sites enables the testing of variation in guideline adherence. The study will also analyze whether differences or similarities in service intensity impacts youth outcomes. Strong inferences regarding differences in youth outcomes are permitted by the rigorous designs used. The combined rigor of these designs will permit analysis of internal validity, construct validity, and reliability of measures and findings, as well as the extent to which guidelines were implemented by JDTCs, and whether there is considerable overlap in the services received by JDTC and TJC youth. As the first rigorous test of the OJJDP Guidelines, findings will yield important and timely feedback to the field as it considers adopting or modifying training and technical assistance for JDTCs, and findings will yield suggestions for how best to translate science into practice.

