**Method:**

OJJDP provided funding for a rigorous multi-site evaluation of the guidelines. This study protocol paper for the Juvenile Drug Treatment Court (JDTC) Guidelines Cross-Site Evaluation presents research designs for the comparison of youth outcomes from 10 JDTCs compared with 10 Traditional Juvenile Courts (TJCs) in the same jurisdictions. Two sites opted into a randomized controlled trial (RCT) and eight sites chose to follow a regression discontinuity design (RDD). Youth data are captured at baseline, and at 6- and 12-month follow-ups using an interview comprised of several standardized assessments. The youths’ official records also are abstracted for recidivism and substance use information. The degree to which the evidence-based guidelines are implemented at each site is assessed via an in-depth court self-assessment collected at baseline and again 2 years later and via structured site visits conducted once during implementation.

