### Data collection procedures

As show in Table 1, data collection is guided by the goals of the study. It involves measures at both the study participant level (i.e., baseline and follow-up interviews, administrative court records) and the site level (i.e., Court Self-Assessment and research site visits). The former measures are specifically focused on comparison of JDTC and TJC interactions with youth (supervision, drug testing, service provision, etc.), which are hypothesized to determine efficacy of JTDC, and the latter measures are focused on understanding the feasibility and degree of implementation of the guidelines and determining whether some have a greater impact than others. Data collection is facilitated by site-based research liaisons (a person local to the research site who is trained on the study procedures and who serves as the first-tier responder to questions from program and evaluation staff), by facilitating communication between the site and evaluation teams to obtain the youth survey data, as well as the abstraction of administrative data from the youths’ juvenile justice records including local and statewide jurisdictions. The data on the implementation of the courts are collected via semi-structured multiple-day site visits by researchers at Carnevale Associates, LLC, and the collection of the Court Self-Assessment data is coordinated by researchers at NPC Research.

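### Court drug-test records, offered as supplementary between-court outcomes and as corroboration of self-report, are confounded by testing frequency wherever JDTC and TJC test at different rates

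*Protocol article*

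**What the plan says.** The abstract (Method) states that the youths' "official records also are abstracted for recidivism and substance use information". The Discussion paragraph on administrative records gives these data two roles.

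- **Between-group outcome.** It says that "specific event dates (e.g., date of a new arrest, date of a positive drug assay) will be recorded", and continues: "This detail enables event history analysis of the relative risk ratios over time between groups". The examples at the end of that sentence are "such as time to first arrest, or number of days of negative drug tests".
- **Corroboration.** It says that the degree to which self-reported group differences, with recidivism and drug use both named, "also are found in the administrative data will enhance the construct validity of research findings regarding the effectiveness of the JDTC programs".

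Other sections treat drug testing as something the courts do. Data collection procedures lists it among the "interactions with youth (supervision, drug testing, service provision, etc.), which are hypothesized to determine efficacy of JTDC". Court self-assessment (CSA) includes it among the content areas on court practice ("drug testing, program/court completion or discharge, data collection"). The Discussion also says: "It is unclear to what extent treatment intensity, court review, family therapy, mental health services, and drug testing will vary between JDTC and TJC".

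Under Primary outcomes, Substance use, the measures are the GAIN-SS substance disorder screener and days of use, both taken from the youth survey. The operational definition is percent days of use over the prior 90 days. No drug test enters it.

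**The concern.** A positive or negative assay exists only when a court orders a test. If one court tests more often, its youth have more opportunities to be found positive, so the first positive comes earlier at the same level of use. They also accumulate more negative results. A between-court contrast on either quantity thus combines two things: how much the youth use and how often the court looks. The article places testing on the exposure side and leaves its frequency by court open. It then reads the resulting dates as outcomes. The paragraph mentions censoring but not unequal ascertainment.

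What is at stake is the supplementary record-based comparison and, more importantly, the corroboration claim. Agreement between records and self-report could be produced by testing intensity, and so could disagreement. The direction would depend on which drug-test metric was chosen.

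**Working it through.** **Inputs.** The article gives no testing rate, positivity or hazard ratio, so there is no figure to reproduce. Assumed: n tests per youth over 12 months; a probability p that any one test is positive, constant and the same in both courts (identical use); and no targeting of tests. Because the article does not define days of negative tests, it is taken here as the number of negative tests.

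**Formulas.**
- Probability of at least one positive in 12 months: 1 − (1 − p)^n.
- Apparent hazard ratio (HR) for first positive, court 1 versus court 2: n1·ln(1 − p) / [n2·ln(1 − p)] = n1/n2. With identical use, p cancels.
- Median time to first positive: (365/n) × ln 0.5 / ln(1 − p).
- Expected negative tests: n(1 − p).

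**Identical use, p = 0.20.**

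| Tests per year, court 1 vs court 2 | Apparent HR, first positive | Expected negative tests |
|---|---|---|
| 26 vs 26 | 26/26 = 1.00 | 20.8 vs 20.8 |
| 26 vs 12 | 26/12 = 2.17 | 20.8 vs 9.6 |
| 52 vs 12 | 52/12 = 4.33 | 41.6 vs 9.6 |

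For 52 versus 12 tests the median times are (365/52) × 3.106 ≈ 22 days and (365/12) × 3.106 ≈ 94 days.

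The hazard ratio does not depend on p, but the 12-month proportion ever positive does. For 52 versus 12 tests it is 93.1% versus 46.0% at p = 0.05, and 99.6% versus 71.8% at p = 0.10.

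**Direction.** The court that tests more looks worse on time to first positive and better on negative tests, although use is the same.

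**Masking of a real effect.** Suppose JDTC truly halves positivity per test, from 0.20 to 0.10. With equal testing the HR is ln 0.90 / ln 0.80 = 0.47. With 26 versus 12 tests it becomes 2.17 × 0.47 ≈ 1.02, so the benefit disappears. With 52 versus 12 it becomes 4.33 × 0.472 ≈ 2.05, so the benefit is reversed.

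**The case against.** The strongest reply is that little of the study depends on this. The primary drug-use outcome is already self-report, and no drug-test outcome is listed under Primary or Secondary outcomes. The Discussion says only that the recorded dates make such analyses possible. Time to first positive assay is implied by the recorded assay dates but never named. Denominators and adjustment could sit in the fuller design document to which the article refers. All of this stands, and it limits the point to supplementary analyses. It does not remove the point, because the corroboration sentence is stated firmly and expressly covers drug use.

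Three stronger readings are tempting, and the article does not support them.

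- A reader might infer that the courts are expected to test at different rates. The article says the extent is unclear, and equal testing, which produces no bias, remains possible.
- A reader might infer that the record comparison measures testing instead of drug use. It mixes the two. If JDTC tested more and still showed later first positives, that would be conservative evidence in its favour.
- A reader might infer that the main drug-use result is biased. It is not, since it comes from the survey.

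It can also be said that testing intensity is captured through the court self-assessments and site visits, and that the Discussion promises control for confounders. The self-assessments and visits describe practice at court level and give no test count per youth. The confounder sentence concerns the interview data. Neither is tied to the drug-test analysis.

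Finally, the article lists youth veracity as a limitation, and drug assays are the biological check on it. That is a real cost of restricting their use. Comparing records with self-report within youth, for concurrent validity, is a separate use that is not a between-court contrast and is not challenged here.

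**Conclusion.** The point holds for the supplementary drug-test comparisons and for the claim that administrative data corroborate between-court differences in drug use. Both are confounded by testing frequency to the extent that testing differs between JDTC and TJC. The apparent hazard ratio under no true difference runs from 1.0 with equal testing, through about 2.2, to about 4.3 across the assumed rates, with negative-test counts pointing the other way. These sizes rest wholly on assumed testing rates, identical use and constant positivity per test. They show how strongly the result can depend on testing, and they are not estimates of bias in this study. The matter deserves correction because it changes what may be concluded from the records. It ranks below an essential correction because the primary outcome is untouched.

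**What to change.** In the Discussion paragraph on administrative records:

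1. Limit the between-group construct-validity claim from administrative data to recidivism.
2. State that dates of positive assays and days of negative tests will not serve as JDTC-versus-TJC effectiveness outcomes. The survey measure remains the between-court drug-use comparison, as already planned.
3. Where the abstracted records allow, report tests given per youth by court as a measure of service intensity.
4. Report the proportion positive per test descriptively, with the caveat that it may still be biased if courts target tests at youth they suspect of using.

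Most of this is a change of wording. The costs are that one biological check on self-report carries less weight, and that items 3 and 4 require a per-youth test count. The section on youth juvenile justice records does not say whether one is abstracted, so this should be confirmed with the sites.
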